# Evaluation of autonomic cardiac modulation and body composition in elderly submitted to the protocol of exercise and the gametherapy: A clinical trial protocol (SPIRIT compliant)

**DOI:** 10.1097/MD.0000000000031236

**Published:** 2022-11-25

**Keywords:** aged, autonomic nervous system, experimental games, gametherapy, heart rate variability

## Abstract

**Objectives::**

Our primary aim is to investigate the cardiac autonomic modulation and body composition of active older adults participating in a physical exercise protocol and gametherapy. Our secondary aim is to assess their functional capacity, cognitive function, balance, respiratory pressures, and functional autonomy.

**Method::**

This randomized clinical trial will include 100 active older adults aged 60 to 80 years. The exercise group (EG) will perform 24 supervised training sessions (strength and aerobic) for 12 weeks (2 60-minutes sessions per week). The gametherapy group (GG) will exercise using gametherapy. Assessments will occur on the first week, after the 12th week, after wash out and in the end of cross over. The primary outcome will be HRV and body composition (bioimpedance). Secondary outcomes will be functional capacity (6-minute walk test), cognitive function (mini-mental state examination), risk of falls and balance (berg balance scale and timed up and go test), inspiratory and expiratory pressures (manovacuometry) and functional autonomy (functional reach test and group of Latin American development to maturity [GDLAM] protocol).

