### 2.3. Sample size

From the 4 factors needed to calculate sample size (i.e., significance level, power, difference between groups, and standard deviation), 2 are unknown (difference between groups and standard deviation) because no previous study used HRV for older adults. Although pilot randomized controlled trials do not require sample size calculations, 15 to 20 participants per group would be necessary to ensure validity. Therefore, we will include 100 participants, 50 participants per group. Our results will provide the information necessary for sample size calculation in future studies.

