### 2.6. Data collection

#### 2.6.1. Assessments plan.

Figure 2 represents the assessment data collection plan. Participants will be assessed in 4 moments: Assessment 1 at the beginning of the protocol, Assessment 2 after 24 sessions, Assessment 3 at the end of the wash-out phase (no intervention for 4 weeks), and Assessment 4 after 24 sessions (crossover phase or switch between protocols).

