#### 2.6.2. Data collection related to the primary aim (HRV) and (body composition).

HRV will be assessed at rest and during exercise using the Polar V800. The Polar V800 is a heart rate monitor that captures electrical impulses from the heart. A device similar to a watch will be placed on participants’ left wrist, and a chest strap with a capture sensor will be positioned on their xiphoid process.

The assessment at rest will describe participants’ cardiac autonomic profile. Participants will be quiet and rest in supine position for 20 minutes in an air-conditioned room (22°C–25°C).

The assessment during exercise will be completed in 2 moments: pre- and post-intervention. The cardiac responses to the different phases of the exercise (i.e., 5-minutes warm-up, 30-minutes aerobic training, 20-minutes strength training of peripheral muscles, and 5-minutes relaxation) will be observed. EG will complete a physical exercise protocol validated by Raimundo et al,^[8]^ and GG will perform gametherapy (Just Dance 2013) Marques et al.^[9]^

HRV will be measured at rest and during exercise using linear methods in the time and frequency domains, non-linear methods, and Poincaré graph. Data analysis will be based on the heart rate recorded during the protocol, and only time series with more than 95% of sinus beats will be used for analysis. After checking for errors, a trace will be selected for analysis and filtered using the Polar Precision Performance SW software (version 4.01.029). Analysis will be performed using the Kubios software.^[9]^

Body composition will be assessed using electrical bioimpedance. Participants will be fasting for 2 hours, with empty bladder (used the bathroom 30 minutes before), and will not have practiced physical activity in the previous 8 hours. OMRON equipment (model HBF-514) will be used; the equipment is composed of a tetrapolar system with 8 electrodes that transmit an extremely low electric current of 50 kHz and 500 µA. Six variables will be recorded: basal metabolism value, body fat percentage, skeletal muscle percentage, body mass index, visceral fat percentage, and basal metabolic rate.

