### 2.12. Statistical analysis

Baseline measures between groups will be compared. The distribution of continuous quantitative variables will be tested for normality and graphically inspected using histograms. A general linear model will analyze differences between groups for the primary and secondary outcomes. If normality assumption is not met, we will proceed with non-parametric techniques (i.e., quantile regression). Effect size (95% confidence interval) and level of statistical significance will be displayed. Missing data will be replaced using multiple imputations. We will minimize potential confounding by adjusting baseline values and controlling other potential confounders. Statistical significance will be set at *P* < .05.

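### The primary outcome is two whole measurement domains under one P < .05 threshold, with no index, recording condition or assessment named, and the stated rationale does not lead to 100 participants

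*Protocol article*

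**What the plan says.** The Abstract (Method) defines the primary outcome by domain: "The primary outcome will be HRV and body composition (bioimpedance").

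Section 2.6.2, whose heading ties it to the primary aim, gives the content of each domain. For HRV: "HRV will be measured at rest and during exercise using linear methods in the time and frequency domains, non-linear methods, and Poincaré graph". The exercise recording covers these phases: "5-minutes warm-up, 30-minutes aerobic training, 20-minutes strength training of peripheral muscles, and 5-minutes relaxation". For bioimpedance: "Six variables will be recorded: basal metabolism value, body fat percentage, skeletal muscle percentage, body mass index, visceral fat percentage, and basal metabolic rate".

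On timing, section 2.6.1 states: "Participants will be assessed in 4 moments". None of the four is marked as the primary one.

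Section 2.12 applies a general linear model to primary and secondary outcomes alike and sets one threshold: "Statistical significance will be set at *P* < .05".

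Section 2.3 says that the group difference and standard deviation are unknown, invokes the position of pilot trials, and concludes: "15 to 20 participants per group would be necessary to ensure validity. Therefore, we will include 100 participants, 50 participants per group".

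**The concern.** A primary outcome should identify one variable, measured one way at one time, or a short list with a rule for combining them. Here the article names two domains. Each holds several variables, and one of them is recorded under several conditions. With a single .05 threshold and no order among the variables, the plan does not say which result answers the primary question. A favourable index could be put forward after the data are seen, and a reader could not tell that it had been selected. The 5% attached to the primary claim would then not be its real error rate.

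The sample-size paragraph adds to this. With no primary variable, the 100 participants are tied to no detectable difference, and the argument offered for 100 points to a different number.

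**Working it through.** **1. Sample size as stated.** Inputs from section 2.3: 15 to 20 per group, two groups, total 100.
- 2 × 15 = 30 and 2 × 20 = 40, not 100.
- To reach 100 by a dropout allowance, N/(1 − d) = 100 needs d = 1 − 40/100 = 60% or d = 1 − 30/100 = 70%. The article states no dropout rate.
- No power calculation can be reproduced, because the difference, the SD and the power value are not given.

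**2. Counting the primary variables.** The article gives no number of HRV indices, so I take the lowest count that the text allows: one index for each of the four families (time domain, frequency domain, non-linear, Poincaré).
- Rest only: 4 + 6 bioimpedance outputs = 10.
- Rest plus four exercise phases: 4 × 5 + 6 = 26.

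Both counts are for one between-group contrast. If the two basal-metabolism entries are one item, they become 9 and 25.

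**3. Chance of at least one false positive.** Assume no true effect and each variable tested two-sided at .05 (the article does not state sidedness). For k independent tests the chance is 1 − 0.95^k. For correlated tests I used equicorrelated normal statistics, Z_i = √r·G + √(1 − r)·E_i, and the probability that any |Z_i| exceeds 1.96. The correlations are assumptions; the article gives none.

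| Tests | r = 0 | r = 0.3 | r = 0.5 | r = 0.8 |
|---|---|---|---|---|
| 2 | 10% | 10% | 9% | 8% |
| 10 | 40% | 35% | 29% | 17% |
| 26 | 74% | 62% | 48% | 24% |

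With 9 or 25 variables the independent values are 1 − 0.95^9 = 37% and 1 − 0.95^25 = 72%, so the duplicated entry hardly matters here. Two primary outcomes tested with Holm (smaller P value against .025, then the other against .05) keep the overall rate at or below 5% for any correlation.

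**4. What 50 per group can detect.** Assume 80% power, two-sided tests, 50 analysed per group and no baseline adjustment.
- At .05: (1.960 + 0.842) × √(2/50) = 0.56 SD by the normal formula; 0.57 SD with the t distribution.
- At .025: (2.241 + 0.842) × √(2/50) = 0.62 SD by the normal formula; also 0.62 SD (0.625) with the t distribution.
- With baseline adjustment the detectable difference is multiplied by √(1 − ρ²). If ρ is assumed to be 0.5 or 0.7, 0.625 SD falls to 0.625 × √0.75 = 0.54 or 0.625 × √0.51 = 0.45.
- With loss it grows. If only 40 per group were analysed (an assumption), it is about 0.625 × √(50/40) = 0.70 SD.

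**The case against.** The strongest reply has four parts.

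*Multiplicity belongs to the analysis plan.* That plan is not shown, so the absence of an adjustment is not a fault by itself. This stands. The choice of primary variable, however, is a protocol decision that the article has already made, as two domains. A later plan would have to narrow a published primary outcome.

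*No success rule is stated.* A reader might infer that any single index below .05 will be declared a primary success. The article does not say so. It promises effect sizes with 95% confidence intervals, and it words parts of the HRV recording descriptively. The percentages above are therefore conditional on each variable being tested at .05. That is the natural reading of section 2.12, but not an explicit rule.

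*The independent figures are too high.* This also stands. Indices from one recording, and outputs of one bioimpedance reading, are plausibly correlated. A reader might conclude that a chance positive is more likely than not, or that dozens of indices are fixed as primary. The text supports neither: at a correlation of 0.5 even 26 tests give just under one half, and the article states no number of indices.

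*The sample is larger than the quoted minimum.* Correct. A reader might infer that 100 is too few or miscalculated. But 50 per group exceeds 15 to 20, section 2.3 admits that the inputs are unknown, and no power is claimed. What fails is the inference, not the number.

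**Conclusion.** The point holds in this form. The primary outcome is fixed as two domains with no index, condition or assessment named, under one .05 threshold. If every variable is tested at .05, the chance of a false-positive primary result is far above 5%: about 17% to 40% for the minimum count of 10, and 24% to 74% for 26. These ranges rest on one index per HRV family, no true effect, two-sided tests and an assumed common correlation between 0.8 and 0. Even the most lenient case in that range is more than three times the nominal level.

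The undefined primary outcome is the part that must be repaired. The step from 15 to 20 per group to 100 is a non sequitur in the rationale and a lesser matter. The bioimpedance list is minor: it appears to name basal metabolism twice, but it does not follow that there are only five variables. One entry may be a mislabelled sixth; the Introduction, for instance, mentions a bioimpedance output that is absent from the list.

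**What to change.** - **Primary outcomes (Abstract, 2.6.2).** Before unblinded data are seen, name one HRV index in one recording condition and one body-composition variable, both at one stated assessment. Resting log RMSSD and body fat percentage would serve as examples; the sponsor may choose others. The assessment must fit the design once the parallel-group description in 2.1 and the crossover in 2.6.1 and 2.8 are reconciled.
- **Testing (2.12).** Test the two with Holm at an overall two-sided .05. Report all other indices as secondary or exploratory, with intervals.
- **Sample size (2.3).** Remove the *Therefore*. Justify 50 per group by feasibility, or by what it can detect with the assumptions stated: with 50 analysed per group and no baseline adjustment, 80% power for 0.57 SD at two-sided .05, or 0.62 SD at .025; smaller with baseline adjustment, larger with dropout. If the pilot framing is kept, the claims should be limited to match.
- **Bioimpedance list (2.6.2).** Clarify whether the two basal-metabolism entries are the same item or one is a mislabelled sixth variable.

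The cost is wording in these sections and a slightly stricter threshold for each primary outcome (.025 at the first Holm step). No participants or measurements are added.

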**Discussion::**

This study will provide relevant information about the effects of physical training (physical exercises and gametherapy) on HRV and other variables in active older adults.

## 1. Introduction

Population aging is a worldwide phenomenon, more than 14% of the population ages over 65 years in most European countries. The concept of successful or active aging first appeared in the 1960s and was associated with physical well-being and satisfaction with life. For a positive aging experience, older adults must actively participate in society, engage in interpersonal relationships, and maintain cognitive function, mental, and physical health. Regular physical exercise and healthy eating habits are crucial to improving cognitive, metabolic, bodily, and cardiac functions in older adults and minimizing aging effects.^[1]^

According to Hong et al,^[2]^ aging is an involuntary and inevitable process that causes progressive structural and functional decrease in body functions, functional capacity, muscle and bone mass, strength, hormones, and cardiovascular function (e.g., decrease heart rate). These losses in function may lead to disabilities, injuries, multiple illnesses, hospitalizations, falls, and mortality.^[3]^ Rezende et al^[4]^ highlight the relationship between advanced age, compromised longevity, decreased muscle strength, and overweight, it’s can be associated a change body composition, induce sarcopenia and fat accumulation, and increase the prevalence of chronic diseases and functional disabilities.

Bioimpedance is a validated instrument to assess body composition (i.e., fat percentage, muscle mass, and bone age). Bioimpedance data can indicate and help to predict chronic degenerative diseases, this instrument became popular over the years due to its low cost and practicality.^[4,5]^ Regarding the cardiovascular system, heart rate and cardiac autonomic activity may decrease with aging. Rajendra et al^[6]^ state that the sympathetic and parasympathetic nervous systems regulate the heart rate, adapting it to different conditions. Increase in heart rate is associated with greater sympathetic than parasympathetic activity. Heart rate variability (HRV) is a safe parameter to analyze autonomic activations responsible for controlling heart rate in multiple physiological and environmental stimuli.^[7]^

Given functional decline associated with aging, more knowledge is needed on the relationship between cardiac autonomic modulation and body composition of older adults submitted to an aerobic and strength exercise and gametherapy.

## 2. Material and Methods

### 2.1. Study design and protocol registration

This is a parallel-group randomized clinical trial registered at REBEC (Clinical Trial registration # RBR-7y24t7t). The research protocol was reviewed and approved by the research ethics committee of Centro de Ensino Superior e Desenvolvimento da Paraíba (#4462499 - CAAE: 39751620.0.0000.5175).

### 2.2. Recruitment and eligibility criteria

#### 2.2.1. Recruitment.

Participants will be recruited by disclosing the study on social media and rehabilitation clinics in Campina Grande and near cities. Potential participants will be contacted by phone to ensure that they meet inclusion criteria. The sample will consist of 100 older adults who meet the eligibility criteria. They will be randomly divided into 2 groups. Figure 1 represents the recruitment process based on the 2010 consolidated standards of reporting trials.

**Figure 1. F1:**
[figure not shown]
Flowchart of participant selection process based on the 2010 consolidated standards of reporting trials (CONSORT).

#### 2.2.2. Eligibility criteria.

Inclusion criteria:

-Physically “active” or “high active” older adults according to the International Physical Activity Questionnaire short form.-People of both sexes aged from 60 to 80 years living in Campina Grande or adjacent cities.-Older adults with diagnosis of chronic degenerative diseases under controlled medication will also be included.

Exclusion criteria:

-Older adults with pathologies impairing the performance of aerobic activities.-Older adults with musculoskeletal disorders impairing participation in the intervention sessions.-Older adults who use walking devices.

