##### 2.6.3.3. Cognitive function.

The Mini-Mental State Examination will assess participants’ mental state and cognitive function. It is a 30-point questionnaire grouped into 7 categories that assess specific cognitive functions, namely orientation to time (5 points), orientation to place (5 points), registration (3 points), attention and calculation (5 points), recall of 3 words (3 points), language (8 points), and visual construction (1 point). Total score ranges from 0 to 30; The maximum score is 30. A score of 23 or lower indicates cognitive impairment. The cutoff is 19 for participants with low educational level.^[13]^

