##### 2.6.3.4. Balance and risk of falls.

The Time Up and Go test will assess participants’ balance, functional mobility, and risk of falls. The test asks participants to get up from an armed chair, walk 3 m, turn around, walk back to the chair, and sit down. According to the time in seconds to complete the test, participants will be classified as without risk of falls (up to 10 seconds), partial dependence and low risk of falls (11–20 seconds), and significant deficit in physical mobility and high risk of falls (over 20 seconds).^[12]^

The Berg Balance Scale will assess participants’ risk of falls and functional dependence. The test consists of 14 predetermined tasks that are common to daily living, each of which is scored on a scale from 0 to 4. The score is based on the time required to perform and maintain a position, perform a task, or reach a distance with the upper limb. The maximum score is 56; higher scores indicate better balance. Scores equal to or lower than 36 are associated with a 100% risk of fall.^[14]^

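### If Berg (and possibly Mini-Mental) scores pile up at their maximum, the quantile-regression fallback would lose power and could return exactly zero despite a real benefit

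*Protocol article*

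**What the plan says.** Section 2.2.2 requires participants to be "Physically “active” or “high active” older adults according to the International Physical Activity Questionnaire short form". It excludes "Older adults who use walking devices" and "Older adults with musculoskeletal disorders impairing participation in the intervention sessions". It also widens entry: "Older adults with diagnosis of chronic degenerative diseases under controlled medication will also be included". The age range is 60 to 80, and no balance or cognitive entry criterion is listed.

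On the Berg scale, section 2.6.3.4 says "The maximum score is 56; higher scores indicate better balance". The same section measures balance by Timed Up and Go in seconds. On the Mini-Mental, section 2.6.3.3 says "Total score ranges from 0 to 30; The maximum score is 30". The abstract lists both scales as secondary outcomes.

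Section 2.12 applies a general linear model to all primary and secondary outcomes, adjusts for baseline values, and then states "If normality assumption is not met, we will proceed with non-parametric techniques (i.e., quantile regression"). It names no quantile and makes no separate provision for bounded scores.

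**The concern.** The entry rules favour mobile, unaided people, who tend to score near the top of a balance scale. A score piled up at its cap is not normal, so the check in section 2.12 would tend to fail and the analysis would pass to quantile regression. If the quantile is the median, that is a poor tool for such data: once more than half of each arm holds the top score, both medians are the top score and their difference is zero.

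At stake is how a null result is read. Both arms receive active training, so improvement is the direction of interest, and improvement is what a ceiling hides. A zero median difference could be reported as exercise and gametherapy being equivalent on that scale, when the summary chosen could not have shown a difference.

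**Working it through.** **What the plan supplies.** The caps are 56 and 30 (sections 2.6.3.4 and 2.6.3.3), and the sample is 50 + 50 = 100 (section 2.3). Section 2.3 says the between-group difference and the standard deviation are unknown. The article gives no baseline score and no share at the cap, so there is no figure of the plan's own to reproduce. Everything distributional below is an assumption, shown over a range.

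**Step 1: when do both medians reach the cap?** If each participant has probability p of scoring the maximum, more than half of an arm of 50 is at the cap with probability P(X ≥ 26), where X ~ Binomial(50, p). For both arms at the same p, square it:

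- p = 40%: 0.0573² = 0.003
- p = 50%: 0.4439² = 0.20
- p = 60%: 0.9022² = 0.81
- p = 70%: 0.9976² = 0.995

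At p = 30% it is below 0.001. This step holds for any capped score, Berg or Mini-Mental.

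**Step 2: would the fallback be triggered?** Take a Berg score as a latent normal value with SD 3, rounded and capped at 56. The share at the cap is 1 − Φ((55.5 − μ)/3). For μ = 54 this is 1 − Φ(0.5) = 31%. For μ = 55, 56 and 57 it is 43%, 57% and 69%. Taking Shapiro–Wilk as the check (the article names no test), one arm of 50 is rejected in 98% of trials with 20% at the cap and in about 100% with 31% or more. Applied to residuals of the baseline-adjusted model at 31%, it rejects in 83% of runs.

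**Step 3: what does the switch cost?** Assume a 2-point latent benefit, a baseline-to-follow-up correlation of 0.7, 50 per arm, baseline adjustment, and 31% at the cap (the μ = 54 setting). Median regression has about 58% power. The linear model it replaces and a proportional-odds model have 97–98%.

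**Step 4: when is the estimate exactly zero?** This uses the same latent SD and correlation, 50 per arm, 200 runs per setting, and regression at the median. Entries are the share of runs with a treatment difference of exactly zero, unadjusted / baseline-adjusted.

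| Baseline share at cap | No effect | +1.5 points | +3 points | −3 points |
|---|---|---|---|---|
| 20% | 0.49 / 0.26 | 0.11 / 0.06 | 0.00 / 0.00 | 0.00 / 0.00 |
| 30% | 0.47 / 0.39 | 0.12 / 0.17 | 0.00 / 0.01 | 0.00 / 0.00 |
| 50% | 0.47 / 0.95 | 0.48 / 0.86 | 0.54 / 0.66 | 0.00 / 0.00 |
| 60% | 0.88 / 0.99 | 0.94 / 0.99 | 0.91 / 0.95 | 0.00 / 0.00 |
| 70% | 1.00 / 1.00 | 1.00 / 1.00 | 1.00 / 1.00 | 0.00 / 0.01 |

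At 60% and above, zero is about as common with a 3-point benefit as with none. At 30% or below with that benefit it is almost never zero, although at 30% the adjusted median estimate shrinks to about 1.3 points. Worsening by 3 points is seen at every level.

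**Step 5: is the information lost from the data or only from the median?** With 60% at the cap and a 3-point latent benefit, the mean difference averages about 0.9 points and the 25th-percentile difference about 1.8. The cap compresses the effect, but the median is what removes it.

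**The case against.** The strongest reply is that the ceiling is inferred. No baseline distribution is given, recruitment runs partly through rehabilitation clinics (section 2.2.1), ages go up to 80, and controlled chronic disease is admitted. That stands, and the point must stay conditional.

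Four stronger readings that a reader might infer are not supported:

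- **That many participants will start at the maximum.** The article does not say so.
- **That eligibility also caps cognition.** Activity level, walking aids and musculoskeletal disorders do not select on it, and section 2.6.3.3 foresees low scores by giving a cutoff of 19 for low educational level. The Mini-Mental shares the cap, not the selection.
- **That the fallback gives zero whatever the effect.** It needs about half or more of each arm at the cap, a beneficial effect, and the median as the quantile. Section 2.12 names no quantile.
- **That the trial would miss any balance difference.** Timed Up and Go in seconds is already collected, and section 2.6.3.2 adds functional reach in centimetres.

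It is also fair that the starting model does well. In unadjusted simulations of the 2-point benefit at latent means 55, 56 and 57, a t-test detects it in about 81%, 74% and 63% of trials and a rank test in 82%, 76% and 67%. The gain over the linear model is therefore small. This helps the plan's first choice but not its fallback, because the stated rule leaves the linear model when normality fails.

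Finally, naming a quantile could be left to an analysis plan. But section 2.12 already fixes which family of method replaces the linear model, for every outcome. The point is that this stated rule suits a capped score badly, not that detail is missing.

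**Conclusion.** The concern holds in conditional form, mainly for the Berg scale and more weakly for the Mini-Mental. If scores collect at the cap, the rule in section 2.12 tends to exchange a model that keeps its power for one that loses it: about 58% against 97–98% at a 31% ceiling. Once about half or more of each arm is at the cap, the median difference can be exactly zero despite real benefit: 54% of unadjusted runs at a 50% baseline ceiling and 91% at 60%, for a 3-point latent gain. These figures rest on an assumed latent SD of 3, a correlation of 0.7, assumed effects of 2 or 3 points, and median regression. The true ceiling share is unknown. No Mini-Mental distribution was simulated; only the binomial step carries over to it directly. Heart rate variability and body composition, the primary outcomes, are unaffected, so the point is minor.

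**What to change.** Leave eligibility and measurements as they are. In section 2.12:

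- For Berg and Mini-Mental scores, replace the quantile-regression fallback with a baseline-adjusted ordinal (proportional-odds) model.
- Report the share of participants at the maximum, per arm and per assessment.
- State that a null result on a scale with most participants at the cap will not be read as equal effect.
- Interpret Berg alongside the Timed Up and Go time already collected. The protocol has no uncapped companion for the Mini-Mental, so for cognition the choice of model and the reported ceiling share are the safeguards.

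The cost is a few sentences and slightly more analysis, with no new participants or tests. The drawback is that an odds ratio is less familiar than a difference in points; the mean difference can be shown next to it.
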